## Abstract

**Background:**

Heart failure (HF) is mainly detected and managed in primary care, but the care is considered suboptimal. We present the rationale, design and baseline results of the Treatment Optimisation in Primary care of Heart failure in the Utrecht region (TOPHU) study. In this study we assess the effect of a single training of GPs in the pharmacological management of patients with HF.

**Methods/design:**

A cluster randomised controlled trial. Thirty primary care practices are randomly assigned to care as usual or intervention defined as a single training in the up-titration and management of HF drug therapy according to the heart failure guidelines of the European Society of Cardiology (ESC). Patients with a GP’s diagnosis of HF will be re-evaluated by an expert panel of two cardiologists and a GP with expertise in HF to come to a definite diagnosis of HF according to the ESC heart failure guidelines. Those with definite HF will be analysed in this study. Drug use will be measured after six months, health status after twelve months, and heart-related hospital admissions and all-cause mortality after two years.

**Discussion:**

Our cluster randomised trial will show whether a single training of GPs improves the pharmacological management of patients with HF and confers beneficial effects on health status after one year, and cardiac hospital admissions and all-cause mortality after two years of follow-up.

**Trial registration:**

ClinicalTrials.gov Identifier NCT01662323

## Background

Heart failure (HF) is an important medical and health care problem with great impact on patient’s health status and life expectancy. The initial diagnosis of HF is mainly made in primary care, and is still often based on the clinical assessment only, irrespective of the general knowledge that such a diagnosis solely based on clinical grounds, without echocardiography bares the risk of both overdiagnosis and underdiagnosis, certainly in the early stages of slow-onset HF [1–4]. This knowledge is also important because a previous study in primary care suggested that uncertainty regarding the diagnosis of heart failure is an important barrier to adequate drug treatment by GPs [5]. Moreover, echocardiography is needed to differentiate HF with a preserved ejection fraction (HFpEF) from HF with a reduced ejection fraction (HFrEF) [1]. Although, both types are part of the heart failure spectrum, the treatment is different. In HFpEF it is focussed on i) release of symptoms with diuretics in case of fluid retention, ii) adequate blood pressure control, and iii) management of comorbidities. Importantly, however, none of these treatments has a clear prognostic benefit and thus lacks a real evidence-base. On the other hand, for HFrEF there are multiple drugs including angiotensin converting enzyme inhibitors (ACE-i) or angiotensin receptor blockers (ARB), β-blockers, and mineralocorticoid receptor antagonists (MRA), and devices that reduce mortality and heart failure hospitalization as it does improve quality of life [1]. Ivabradine should be considered in the subgroup of patients who remain symptomatic with the three aforementioned drugs, and have sinus rhythm with a pulse frequency higher than 70 beats/min in rest [1].

**Table 1 Tab1:** The diagnosis of heart failure according to the ESC guidelines on heart failure 2012 [1]

Diagnosis of HF with a reduced ejection fraction (HFrEF)	Diagnosis of HF with a preserved ejection fraction (HFpEF)
Symptoms typical of HF	Symptoms typical of HF
Signs typical of HF^a^	Signs typical of HF^a^
Reduced left ventricular ejection fraction	Normal or only mildly reduced left ventricular ejection fraction and left ventricle not dilated
	Relevant structural heart disease (LV hypertrophy/left atrial enlargement) and/or diastolic dysfunction

*HF* heart failure

^a^Signs may not be present in the early stages of heart failure (especially in HFpEF) and in patients treated with diuretics

Previous studies showed that general practitioners (GPs) are less successful than cardiologists in up-titrating HF drugs according to guidelines [2, 3, 6–9]. Nevertheless, they adequately maintain the drug management initiated in secondary care, as good as done in heart failure clinics [10, 11].

We aim to determine whether a single training of GPs focused on the drug management improves the pharmacological management of patients with definite HF, HFrEF and HFpEF seperately. Additionally, we determine if it has a beneficial effect on health status, cardiac hospital admissions, and all-cause mortality.

### Key objectives

To assess how many patients labelled with HF in primary care really have heart failure.To assess the effect of a single half-day training on drug management in heart failure on drug use, health related quality of life, heart failure hospitalizations, and all-cause mortality after six months, 12 months, and 24 months, respectively.

## Methods

### Study design

We designed a cluster randomised trial with randomisation at the level of the primary care practices, to help prevent contamination with the intervention. Thirty practices are randomly divided into two groups of fifteen. The intervention group will receive a half-day training on HF management and will receive an up-titration chart for daily use in the management of HF patients during the study, while the control group will not receive specific training, and provides care as usual. The study starts with the training, and participants in both groups will be followed up for two years. After six months of follow-up the electronic medical files will be scrutinized for (change in) prescriptions of drugs in comparison to baseline. Twelve months after the training the participants will be sent a questionnaire on health status. After two years, hospital admissions and all-cause mortality will be assessed, by again scrutinizing the GPs’ electronical files (Fig. 1).

**Fig. 1 Fig1:**
[figure not shown]
Study scheme. ICPC = International Classification in Primary Care, PCP = primary care practice; HFrEF = heart failure with reduced ejection fraction, HFpEF = heart failure with preserved ejection fraction, rs-HF = isolated right-sided heart failure. SF-36 and EQ-5D are health related quality of live questionnaires. T0: start of the study with training of the GPs, GP trainees and practice nurses of the intervention group. T1: Six months of follow-up; assessment of cardiovascular drug use in both groups in comparison to baseline. T2: Twelve months of follow-up; questionnaires on health status (SF-36 and EQ-5D will be filled out by participants in both groups. T3: Two years of follow-up; assessment of hospitalisations and all-cause mortality in the electronic medical files of the GPs in both groups

**Fig. 2 Fig2:**
[figure not shown]
Up-titration scheme as provided on a leaflet to be used in everyday practice by the GPS in the intervention group

### Recruitment of general practitioners

General practitioners (GPs) will be recruited in and around Amersfoort, a city in the centre of the Netherlands. A representative group of 195 GPs working in group, duo or solo practices in urban, suburban, and rural areas were invited by letter. Forty-five GPs working in 30 GP practices consented to participate. They are all familiar with the Dutch GP guideline on heart failure [12]. The participating general practices were randomly allocated to either the intervention or care as usual group. The project manager undertook randomisation in a blinded fashion. GPs working in one practice were allocated to the same group, to avoid contamination of GPs and participants between the two groups, which can occur if randomization is performed at an individual participant level.

### Study population and recruitment

All citizens in the Netherlands are registered with a GP, also those who receive cooperative care from a medical specialist, except those living in a nursing home or hospice. All patients enlisted with the participating GPs and who have a GP’s diagnosis of HF encoded according the International Classification of Primary Care (ICPC) code K77 will be assessed if this ICPC code was allocated at least twice for patient contacts, to prevent single accidental miscoding. Five months before the start of the study, the electronic medical files of the 30 participating GPs will be scrutinised for such patients labelled with ICPC code K77, and if echocardiographic results are missing, the GPs of both groups will be urged to consider referral for echocardiography. The start of the study is the date of training of the GPs in the intervention group. An expert panel consisting of two cardiologists and an experienced general practitioner will evaluate all available diagnostic information from the electronic medical files of the GPs, including echocardiography results mentioned in cardiologist’s papers when this investigation was performed. They decide whom of those with ICPC code K77 has definite HF, probably or possibly HF, or no HF according to the European Society of Cardiology guidelines [1]. Only patients who have definite HF according to the panel will be analysed in the cluster randomised trial. All participants will be asked to give written informed consent.

### Sample size

We base our sample size calculation on the cases with definite HFrEF. We speculate that 30 % of them will be on a β-blocker and 60 % on an angiotensin converting enzyme inhibitor (ACE-i) or angiotensin receptor blocker (ARB) at baseline, and that after six months of follow-up after the training session these percentages will have increased to 60 and 90 %, respectively in the intervention group, while remaining the same in the control group. To prove a difference of 30 % in prescription rates in ACE-i/ARBs and β-blockers between the intervention and care as usual arm after six months with an alpha of 0.05, a power of 0.80, and an intra-cluster correlation coefficient of 0.05 [12], and a cluster size of 5, we need 47 patients with HFrEF in each study arm. Considering a drop-out of 10 % we aim to include 52 participants in each arm (total 104). We calculated that around 30 general practices should participate to recruit 104 patients with definite HFrEF.

### Intervention and care as usual

GPs, GP trainees, and nurse practitioners of general practices of the intervention arm receive a two hours lasting interactive training on the diagnosis and pharmacological management of HF by a cardiologist and GP with expertise in HF. Special attention will be paid to initiation and up-titration to optimal dosage of evidence-based drugs in patients with HFrEF, especially in the drugs that should always be considered to be prescribed; ACE-inhibitors or ARBs, beta-blockers, and MRAs. The ‘hand-out’ leaflet to be used in everyday practice will be explained (Fig. 2). This leaflet provides detailed information on the intervals in the up-titration, what should be checked at control visits, contra-indications of the cardiovascular drugs, and laboratory tests needed (i.e., creatinine and potassium levels). Differences in the drug management of patients with HFrEF and HFpEF will be explained, as also the most common interaction and adverse effects of HF drugs. Finally, general aspects such as adherence, and polypharmacy and options of self-care will be discussed interactively. Participants of the training will not be reinforced by reminders, newsletters, or other communications after the training. GPs, GP trainees and practice nurses in the care as usual group will not receive such a training nor an up-titration chart.

### Panel procedure and the definite diagnosis of heart failure

The expert panel will consist of two cardiologists and a GP experienced in HF. They will decide during consensus meetings on the presence or absence of HF following the criteria of the HF guidelines of the ESC (Table 1). In addition to symptoms and signs suggestive of HF additional evidence from echocardiography of structural or functional abnormality of the heart at rest is needed to establish the presence of HF [1]. With the assumption that all patients labelled with a GPs diagnosis of heart failure have symptoms and signs suggestive of HF, the panel will evaluate, when available, the results from additional diagnostic testing such as natriuretic peptide values, chest X-ray, electrocardiography and echocardiography. Based on consensus, the panel decides if a patient has no HF, probably or possibly HF, or definite HF. Only patients with definite HF according to the panel will be analysed in the cluster randomized trial.

Cases with definite HF will further be subdivided in HFrEF, HFpEF, and isolated right-sided HF (rs-HF). For HFrEF, a reduced left ventricular ejection fraction (LVEF) is needed, arbitrary ≤ 45 %. For HFpEF, the LVEF should be normal or nearly normal, arbitrary >45 %, this in the presence of at least two structural or functional abnormalities related to relaxation such as a left atrium volume indexed (LAVI) >34 ml/m^2^, E/e’ >15, E/A <0.75, and/or a left ventricular wall thickness >11 mm. In those with atrial fibrillation, a LAVI >34 ml/m^2^ is sufficient for the diagnosis of diastolic dysfunction. For isolated right-sided heart failure, the LVEF should be >45 %, and the calculated peak pulmonary pressure >40 mmHg that is insufficiently explained by left ventricular dysfunction.

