### Outcomes

Study outcomes are the proportions of patients labelled with ICPC K77 who really have heart failure according to the expert panel, and the proportion of patients with definite heart failure and a reduced ejection fraction that received the most relevant and universally needed HF drugs, including ACE-i/ARBs, β-blockers, and mineralocorticoid receptor antagonists. Drug use at baseline and after six months will be compared between the two groups.

Health status will be assessed with the SF-36 and the EQ-5D in all with definite HF (HFrEF and HFpEF). The SF-36 is subdivided into eight domains: physical functioning, social functioning, limitations in usual role activities due to physical problems, limitations in usual role activities due to emotional problems, bodily pain, general vitality health, general mental health, general health perception. Scores range from 0 to 100. The EQ-5D questionnaire has five dimensions: mobility, self-care, usual activities, pain/discomfort, and anxiety/depression, which are divided into three degrees of severity; “no problem”, “some problems” or “major problems”. A single index score can be produced using information from these five dimensions. Higher scores on both questionnaires are associated with a better health-related quality of life.

Also cardiac and other hospitalisation will be assessed in all with definite HF, and the duration of hospitalisation.

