### Data analyses

We will calculate with its 95 % confidence interval how many patients with an ICPC code K77 were correctly diagnosed with heart failure according to the expert panel.

The proportion of prescribed HF drugs between the two groups will be compared after six months taking into account baseline differences. The difference in health status between participants with definite HF in the two study arms at 12 months will be compared with ANCOVA. Differences between participants of the two groups regarding hospitalisations and all-cause mortality will be assessed after two years. A multilevel approach will be used in the analyses to correct for the fact that we randomized at the GP practice and not at the patient level.

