There are several limitations to be mentioned. First, a two-hour training is short to adequately train GPs how to initiate and up-titrate heart failure medication in patients with HFrEF, even if they are familiar with heart failure guidelines, receive a helpful leaflet, and with over half of the patients receiving cooperative care from the cardiologist. For logistical and practical reasons we choose for such a single intervention because it resembles most closely post-graduate education GPs receive in the Netherlands. Secondly, we measure outcomes only once; drug prescriptions after 6 months, hr-QoL after 12 months, and CV morbidity and mortality after 24 months. More frequent measurements of outcomes would result in ‘disturbing’ GPs, and multiple times filling out questionnaires by participants. It would easily result in ‘drifting away’ from ‘real’ care as usual of those in that arm of the study. Thirdly, not all patients will undergo echocardiography in this practice-based study. The advantage of a practice study is the inclusion of ‘real’ patients and the assessment of drugs in ‘real’ practice. The downside is missings on some variables. In real live practice not everybody labeled with heart failure underwent echocardiography. Nevertheless, for our cluster randomized trial we will selectively analyse those with definite HF, that is, symptoms of HF and functional/ structural abnormalities with echocardiography, evaluated by an expert panel of two cardiologists and a GP. Fourthly, we evaluated both HFrEF and HFpEF patients, although, for HFpEF ‘clear’ evidence-based treatment is lacking. Nevertheless, HFpEF is part of the heart failure spectrum, and has nearly as poor a prognosis as HFrEF. Moreover, these patients suffer of symptoms, notably fluid retention causing shortness of breath and peripheral oedema. These symptoms can adequately managed with diuretics. Physicians should realize that symptom relieve is of utmost importance in these patients by titrating the dose of diuretics as optimally as possible. Adjustments of diuretic dose to filling status is really the ‘art’ of medicine. Even more can be done in patients with HFpEF; blood pressure and comorbidities should be adequately managed according to the ESC guidelines 2012. Finally, the recommendation to GPs in both trial arms to refer for echocardiography before the training may increase awareness of HF diagnosis and management and may dilute the effect of the intervention. 

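### The panel takes the symptoms-and-signs part of its HF standard from the GP label it is meant to validate; taken alone, this can only raise the confirmed proportion or leave it unchanged, by an amount that cannot be computed

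*Protocol article*

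**What the plan says.** All references are to the protocol article.

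- **Key objectives.** The first objective is "To assess how many patients labelled with HF in primary care really have heart failure".
- **Outcomes and Data analyses.** The matching outcome is "the proportions of patients labelled with ICPC K77 who really have heart failure according to the expert panel". The analysis gives, with a 95% confidence interval, "how many patients with an ICPC code K77 were correctly diagnosed with heart failure according to the expert panel".
- **Panel procedure, the standard.** Both components are required: "In addition to symptoms and signs suggestive of HF additional evidence from echocardiography of structural or functional abnormality of the heart at rest is needed".
- **Panel procedure, the assumption.** The next sentence begins "With the assumption that all patients labelled with a GPs diagnosis of heart failure have symptoms and signs suggestive of HF" and goes on to say that the panel weighs natriuretic peptides, chest X-ray, ECG and echocardiography where these exist.
- **Discussion.** The analysis set is described as "definite HF, that is, symptoms of HF and functional/ structural abnormalities with echocardiography, evaluated by an expert panel".
- **Study population and recruitment.** The panel is said to assess all the diagnostic information in the GP file. A patient is considered only "if this ICPC code was allocated at least twice for patient contacts, to prevent single accidental miscoding".
- **Table 1 footnote (Background).** "Signs may not be present in the early stages of heart failure (especially in HFpEF) and in patients treated with diuretics".

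**The concern.** A validation study needs a reference standard that does not borrow from the label being validated. Here the echocardiographic component is independent of the GP label, but the clinical component is inferred from it. A K77 patient with a structural abnormality and no heart failure symptoms has, on the stated assumption, no clinical criterion left to fail. The confidence interval would not show this error, because it reflects sampling variation only.

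The article also gives two accounts of the same step. Under the panel procedure, symptoms are assumed; in the Discussion, they are part of what the panel evaluates. A reader of the results would not know which was done, and the listed limitations do not mention the assumption.

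Two things are at stake. One is the meaning of the first outcome. The other is the make-up of the trial population, since only patients with definite HF are analysed in the cluster randomised comparison.

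**Working it through.** **The plan's own figures.** The article gives no expected value or precision for the proportion of K77 patients with HF, so there is no figure to reproduce for this outcome. The only design figure is 47 HFrEF patients per arm. It reproduces with 30% versus 60%, two-sided alpha 0.05 (sidedness assumed), power 0.80 and unpooled variance: 39.24 per arm × design effect [1 + (5 − 1) × 0.05 = 1.2] = 47.09. This point does not affect it.

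**Direction, with echocardiography complete.** The stated standard is P(echo criterion and symptoms/signs). With the clinical part assumed, the panel estimates P(echo criterion). A joint probability cannot exceed either of its components, so the assumption either raises the proportion or leaves it unchanged.

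**Size.** Let e be the share of K77 patients who meet the echo criterion, and u the share of those who truly lack the clinical component. The overstatement is e − e(1 − u) = e × u. The documents give neither e nor u. With assumed values, in percentage points:

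| e | u = 0 | u = 5% | u = 10% | u = 20% |
|---|---|---|---|---|
| 50% | 0 | 2.5 | 5 | 10 |
| 60% | 0 | 3 | 6 | 12 |
| 70% | 0 | 3.5 | 7 | 14 |
| 80% | 0 | 4 | 8 | 16 |

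**Missing echocardiography.** The Discussion says that not every patient will have an echocardiogram. Let m be the share without one (not given). Assume that such patients cannot be classed as definite and that missingness is unrelated to true status. The panel then finds (1 − m)e, the true proportion is e(1 − u), and the net error is (1 − m)e − e(1 − u) = e(u − m). It is negative whenever m exceeds u. For e = 60% and u = 10%:

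- m = 0: 0.6 × 0.10 = +6 points
- m = 10%: 0.6 × 0 = 0 points
- m = 20%: 0.6 × (−0.10) = −6 points

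**What reporting both ways would show.** In the last case the panel figure is 0.8 × 0.6 = 48%. Requiring symptoms, if documentation were perfect, gives 48% × 0.9 = 43.2%. The gap of 4.8 points is the effect of the assumption. The true value is 0.6 × 0.9 = 54%, above both. The two figures therefore bound this one assumption and not the true proportion, which is why the share without echocardiography must be reported beside them.

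**The case against.** The strongest case on the other side has five parts.

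- **The objective component is never assumed.** Echo evidence is still required, and a K77 patient can still be classed as having no HF or only probable or possible HF. The Background's worry about overdiagnosis concerns clinical diagnosis without echocardiography, and the panel supplies exactly that check. This stands: calling the whole outcome circular goes too far. It does not cover patients with an abnormality and no symptoms.
- **Miscoding is partly handled.** The code must appear at least twice. This removes isolated coding slips, but not a mistaken label that is carried forward.
- **The panel is not a mechanical echo rule.** It decides by consensus, on several tests, and the wall-thickness and left-atrial thresholds subdivide cases already judged definite. This stands: nothing says that two echo findings alone make a patient definite. But no stated step restores a check on symptoms.
- **Absent signs need not mean a false label.** The Table 1 footnote allows HF without signs. It excuses signs only, not symptoms.
- **Requiring documented symptoms has its own bias.** True cases with sparse notes would be demoted. This stands, and it argues against changing the main classification.

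A reader might go further and infer that the proportion is in fact inflated, for instance by 1.5 to 12 points, taking 5 to 20% of K77 patients without documented symptoms or signs and 30 to 60% of those with a qualifying echo (0.05 × 0.30 = 0.015; 0.20 × 0.60 = 0.12). The documents do not support this. Both inputs are guesses, the range excludes zero without reason, and it treats undocumented as absent.

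**Conclusion.** The point holds in a limited form. The panel procedure takes one component of its reference standard from the label that the first objective is meant to validate, and this conflicts with the Discussion's account of definite HF. Taken alone, the assumption biases the proportion upward or not at all. The size cannot be derived from the documents: it is 0 to 16 points over the assumed ranges (e from 50 to 80%, u from 0 to 20%). Once missing echocardiography is counted, the net error can have either sign.

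A reader might also infer that wrongly included patients dilute the trial's health-status, admission and mortality results. That is plausible, since definite HF defines the analysis set, but no figure in the article shows it. The assumption applies to both arms, and the HFrEF drug-use outcome still requires an LVEF of 45% or less, although a patient with low LVEF and no symptoms could enter it.

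**What to change.** 1. Keep the panel's classification as primary. Add one item to its form: for each K77 patient, are typical symptoms documented in the file under review, and signs too, subject to the Table 1 footnote?
2. Report the K77 proportion without and with a requirement for documented symptoms, as upper and lower bounds for this assumption only. Report the share without echocardiography beside them.
3. Describe the main figure as the proportion of K77 labels with objective confirmation, given assumed symptoms and signs.
4. Repeat the trial analyses in patients with definite HF and documented symptoms, as a sensitivity analysis.
5. Reconcile the recruitment section, the panel procedure and the Discussion, so that they give one account of whether symptoms are assumed or assessed, and list the assumption among the limitations.

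The cost is one extra item taken from files already being read. The drawback is that the lower bound will also reflect poor documentation, and this should be stated when it is reported.
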